#### Deviations from original random assignment

In December 2008, before the baseline survey had commenced, but simultaneous with the treatment villages receiving their grant (but not before services began), a World Bank team uncovered that five districts had not complied with the village level randomization. Specifically, this meant that these districts took action to implement the project in an order that was different to what was originally agreed to with the MoNE and the World Bank in 2006. The main reason stated by the districts for their lack of compliance to the randomization was convenience – they felt it was easier to roll-out the project to villages that were proximate rather than complying with the randomization design which did not allow for clustering project sites. The districts that did not comply are shown in the participant flow diagram (Figure 1) with the number of villages that remained in the original batch to which they were assigned. Note that full compliance would mean ten villages in each group and no changes.

### Sample size calculation

The average treatment effects at the village level, using a cluster randomized design, drove the sample size calculations for this experiment. It was challenging to estimate baseline variations between and across clusters for the outcome measures and to set minimum detectable effect sizes as a project of this kind was unprecedented in Indonesia, and none of the intended outcome measures had ever been collected in the country. Thus, the research team used a combination of education measures in Indonesia and ECED measures from a similar project in a country with comparable socioeconomic indicators, the Philippines.

In order to estimate changes in comparable outcome measures, the team calculated the intracluster correlation using net enrolment ratios in junior secondary education as observed in the 2004 Indonesian national household survey (Susenas). We used secondary rather than primary enrolment due to Indonesia’s near universal enrolment at the primary level. In general, one enumeration area in Susenas is a village, and in each area, 16 households are interviewed. The intracluster variation between enumeration areas for junior secondary enrollment was estimated at 0.23, which was used in the subsequent power calculations.

To predict our effect sizes for the sample calculations, we used results from a study conducted in the Philippines on the impact of a comparable, community-based ECED project [31]. The study evaluated an ECED initiative of the Philippine Government using longitudinal data collected over 3 years on a cohort of 6,693 children aged 0 to 4 years at baseline. The Philippine ECED program was especially relevant for this study as the Indonesian program was modeled on the Philippine example. The Philippine ECED program included a range of health, nutrition, early education and social service programs, and aimed to improve the survival and developmental potential of those children who were most disadvantaged and vulnerable. The Philippine ECED project did not introduce new services, but provided a child development worker to each of the program areas to link center-based and home-based services in an integrated multi-sector approach [32].

The Philippines study used outcome measures relating to gross motor skills, fine motor skills, expressive language, receptive language, cognitive skills, self-help and social-emotional development, and reported mostly positive impacts in the range of 0.3 to 1.1 standard deviations [32]. Using these impacts as the minimum detectable effect sizes for the Indonesian study, the minimum number of villages to sample was in the range of 7 to 116 villages, depending on the chosen outcome measure, with half of this sample to be allocated to the treatment group and half to the control. We calculated the minimum number of clusters on the basis of a power of 0.9, with an estimated intracluster correlation coefficient (ICC) of 0.23 and with the requirement of ten children surveyed per village. The Philippines study, however, reported unusually high effect sizes especially when compared to a review (published after the sampling for this study) by Nores and Barnett [33], which suggested an average effect size of 0.255 standard deviations for studies investigating the impact of cash transfers, nutritional, educational or mixed interventions conducted in low and middle income countries. Using this as the minimum detectable effect, keeping all else constant, the minimum number of villages required increases to 182. The study eventually sampled 200 villages randomized into treatment and control groups. The power calculations suggest that this would be more than sufficient to detect impact estimates in similar size to those that are reported for the Philippine ECED intervention, and just sufficient to detect the average effects reported in Nores and Barnett’s review.

The size of the matched control group was set equal to the treatment group. In the analysis, we will also be able to present estimates of the impact that rely on standard difference in difference assumptions, comparing the treatment group with the matched control group. The sample size calculations as discussed above are valid under these assumptions; hence the same sample size for the matched control group.

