##### Study hypotheses

The overarching goal of the ECED program is to improve poor children’s overall development and readiness for further education within a sustainable quality ECED system. However, for the purposes of the trial we required more specific aims and thus developed the following hypotheses. Relative to the non-intervention group, participants in the experimental group of the study will:

1) Have greater access to ECED services.

2) Have a higher participation rate in ECED services.

3) Have a higher enrolment rate in school at earlier ages.

4) Be more ‘school ready’.

5) Have higher community awareness about the importance of ECED.

6) Have higher persistent breastfeeding rates, improved nutrition and improved early childhood stimulation.

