#### Matched control sample

Due to concerns that the randomization and/or planned timelines of implementation would not be adhered to, the research design also incorporated ten matched control villages per district. The matched controls were identified by asking district officials to identify ten control villages that were not part of the ECED project (that would never receive the treatment), but otherwise were similar to the ten randomly selected treatment Batch 1 villages. The rationale for two control groups was practical – to reduce the risk of not being able to identify impact because of unforeseen implementation challenges. It was also technical – 18 months (the anticipated gap between Batch 3 and Batch 1) was thought to be potentially insufficient to detect significantly different child development outcomes, and thus the matched controls were to allow for comparison over 3 years between baseline and endline rather than just the 18 months with the randomized control. One potential implementation challenge, as is common during implementation, was that the project would start late and accelerate as implementation progressed. This would mean that less than 18 months may elapse before controls received the treatment. Thus, we included the matched controls, which aimed to make the study less vulnerable to changes in timing and enabled tracking of longer-term impacts. In sum, the project design was to make use of one treatment group of 100 villages and two control groups, each consisting of 100 villages, thus 300 sample villages in total.

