Our approach to manage this issue is two-fold. For the utilization variables, which we believe responded quickly to the opening of early childhood development services, we intend to reconstruct a variable of utilization before the start of the project based on retrospective data collected in the baseline survey. For child development variables, we intend to use the baseline data to estimate the impact of the intervention after 6 months comparing Batch 1 to Batch 3 villages.

The consequence of the late midline survey is more limited. When conducting the midline analysis in (3), the comparison is no longer between 18 months of implementation and no project, but rather between 20 and 9 months of implementation. This is because project implementation was delayed in Batch 3. By the time the midline data were collected, Batch 3 villages had been implementing the intervention for only 9 months. Therefore, we intend to use the midline data to estimate the impact of the project after Batch 1 villages have received the project for 20 months and Batch 3 villages have received the project for 9 months, that is, the impact of 11 months of differential exposure. For outcome variables which respond quickly to the treatment, such as utilization, this is a problem as both Batch 1 and Batch 3 villages received treatment. Our strategy will be to focus on utilization variables which capture utilization over the entire evaluation period, not only at the time of the survey. For outcome variables which respond more slowly to the treatment, such as child development outcomes, we simply report the comparison as above, indicating that this is the impact of the 18-month difference in treatment duration.

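### The stated power of the 200 randomised villages assumes the arms differ by a full programme effect; it does not carry over to the midline contrast of 20 v 9 months of exposure

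*Protocol article*

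**What the plan says.** The Study hypotheses section compares the programme with an untreated group: "Relative to the non-intervention group, participants in the experimental group of the study will" show better results on six counts.

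The Sample size calculation section takes its effect sizes from two sources:
- **A Philippine programme evaluation**, with impacts of 0.3 to 1.1 SD. "The study evaluated an ECED initiative of the Philippine Government using longitudinal data collected over 3 years".
- **A review of interventions in low and middle income countries**, published after sampling, which "suggested an average effect size of 0.255 standard deviations".

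The number of villages was worked out "with an estimated intracluster correlation coefficient (ICC) of 0.23 and with the requirement of ten children surveyed per village", aiming for 90% power. The section then says of the 200 randomised villages that they more than suffice for the Philippine effects and are "just sufficient to detect the average effects reported in Nores and Barnett’s review".

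Other sections describe a different randomised contrast:
- **Matched control sample:** even the planned 18-month gap between Batches 1 and 3 "was thought to be potentially insufficient to detect significantly different child development outcomes".
- **Planned analyses:** the effect is expected to depend on how long a village has had the project, and the randomised control is of limited value for the end-of-project impact because it will have been treated by then.
- **Deviations from planned design and consequences for analysis:** at midline "the comparison is no longer between 18 months of implementation and no project, but rather between 20 and 9 months of implementation". The same section calls this 11 months of differential exposure, and the Discussion repeats the figure.

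No section restates power for that contrast.

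**The concern.** The power statement is attached to the randomised villages and uses effects of programmes. By the protocol's own reasoning, the randomised arms at midline deliver only the part of the effect that comes from Batch 1's extra 11 months. The difference to be detected is then likely to be smaller than the one used for sizing.

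Equation (3) at midline is presented as needing minimal assumptions, so readers will give it weight. Someone who takes the stated power at face value could read a non-significant midline result as evidence against an effect of the size seen elsewhere. The design may have been unlikely to detect such an effect against a control arm already nine months into the project.

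The closing sentence of the deviations section makes this misreading more likely. After setting out the 11-month difference, it says that slowly responding outcomes will be reported as reflecting an 18-month difference.

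**Working it through.** **Inputs.** From the Sample size calculation section: ICC 0.23, ten children per village, equal allocation, 200 villages, power 0.9, effect 0.255 SD. From the deviations section: 20 v 9 months at midline. Assumed: two-sided 5% (alpha is not stated), full compliance, no gain from covariates, normal approximation.

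**Step 1: the plan's own claim.**
- Variance of a village mean = 0.23 + 0.77/10 = 0.307 SD².
- Standard error of the difference, 100 v 100 villages = √(0.307 × 2/100) = 0.0784 SD.
- Power for 0.255 SD = Φ(0.255/0.0784 − 1.96) ≈ 0.90.
- Difference detectable with 90% power = (1.960 + 1.282) × 0.0784 = 0.254 SD.

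The verbal conclusion reproduces for a true between-arm difference of 0.255 SD. The printed minimum of 182 villages does not: 4 × (3.242/0.255)² × 0.307 ≈ 198. That is a separate matter and does not affect what follows.

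**Step 2: how much slack there is.** This needs no dose-response model. The difference detectable with 80% power is (1.960 + 0.842) × 0.0784 = 0.220 SD, and 0.220/0.255 = 0.86. Even 80% power requires the midline contrast to keep about 86% of the full effect although the control has had 9 of Batch 1's 20 months.

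**Step 3: illustrative dilution.** Assume that effect is proportional to exposure and that the programme effect is reached at T months. The midline contrast is then the effect × 11/T.

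| T (months) | Contrast for 0.255 SD | Power, 10 per village | Power, 20 per village | Programme effect detectable at 90% (10 per village) |
|---|---|---|---|---|
| undiluted | 0.255 | 90% | 94% | 0.25 SD |
| 18 | 0.255 × 11/18 = 0.156 | 51% | 57% | 0.254 × 18/11 = 0.42 SD |
| 20 | 0.255 × 11/20 = 0.140 | 43% | 48% | 0.254 × 20/11 = 0.46 SD |
| 36 | 0.255 × 11/36 = 0.078 | 17% | 19% | 0.254 × 36/11 = 0.83 SD |

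The 20-per-village column uses the households actually sampled (Sampling procedures): variance 0.23 + 0.77/20 = 0.2685, standard error 0.0733.

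For the low end of the Philippine range (0.3 SD, ten per village), power falls from 97% undiluted to 65%, 56% or 21% with T = 18, 20 or 36.

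**Step 4: the comparison with matched controls.** For 100 v 90 villages the standard error is √(0.307 × (1/100 + 1/90)) = 0.0805, and power for 0.255 SD is Φ(0.255/0.0805 − 1.96) ≈ 0.89. Those controls never receive the project, so this contrast is not diluted. It is not randomised.

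**The case against.** Several points on the other side are sound.

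- **The power sentence is conditional and, for its condition, correct.** A true 0.255 SD difference between arms has about 90% power. The calculation is dated December 2006, before the delays. But the section was later extended with a review published after sampling, and it still makes no allowance for a treated control.
- **A reader might infer that midline power is 43%.** The documents do not support any single figure. They give no dose-response shape and no exposure length behind 0.255 SD, and the three years quoted for the Philippine study describe data collection. Early saturation would make the contrast smaller still. A late threshold could make it larger, up to the full effect if nothing has emerged by nine months.
- **A reader might infer that equation (3) at midline is the only randomised comparison.** It is not. The deviations section also plans Batch 1 v Batch 3 at baseline, after about six months and against a control not yet treated. Its exposure gap is shorter still, so it does not rescue the power claim.
- **A reader might infer that the claim fails for the whole Philippine range.** It does not. With 20-month scaling, effects above about 0.46 SD keep 90% power.
- **A reader might infer that the main objective is underpowered.** That comparison is Batch 1 v matched controls. It is undiluted and has about 89% power, although the Discussion concedes a threat to its internal validity.
- **The limitation is disclosed in words.** The Matched control sample section and the Discussion say that the short gap may be too little to show an impact, and dosage measures are planned. These caveats neither revise nor quantify the power statement, which stands unqualified.

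**Conclusion.** The concern holds in a limited form. The power claimed for the 200 randomised villages applies only if the arms differ by the full programme effect, and at midline the protocol says they differ by 11 months of exposure. The claim therefore does not transfer to equation (3).

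The firm result is a detectable between-arm difference of about 0.25 SD at 90% power, with no slack at 0.255 SD. The size of the shortfall is conditional: about 17% to 51% power for a 0.255 SD programme effect under proportional dose-response with that effect reached between 36 and 18 months (19% to 57% with 20 children per village). All figures rest on the stated ICC, an assumed two-sided 5% level and full compliance.

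**What to change.** In the Sample size calculation section:
1. State that 200 villages detect a between-arm difference of about 0.25 SD with 90% power, and state the alpha used.
2. For Batch 1 v Batch 3 at midline, give the power range for 11 months of differential exposure together with the dose-response assumption behind it, and withdraw the claim that the sample just suffices for 0.255 SD.
3. Limit the claim that the sample more than suffices to programme effects above roughly 0.46 SD (20-month scaling) or 0.83 SD (36-month scaling).
4. Say that the comparison with matched controls is not diluted in this way and is not randomised.

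In the analysis text for equation (3), state that a non-significant estimate will be read from its confidence interval as the effect of 11 months' differential exposure, not as absence of a programme effect. On the stated inputs the half-width is about 1.96 × 0.0784 = 0.15 SD. Reconcile the closing sentence of the deviations section, which calls the difference 18 months.

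The cost is wording, a short recalculation and a less favourable power figure in print. No villages, data or estimators change.

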#### Sampling procedures

The steps taken to obtain the final list of sampled villages are described in the Recruitment section above. The baseline survey contained 310 villages, of which 100 were originally allocated to Batch 1, 20 originally allocated to Batch 2, 100 originally allocated to Batch 3 and 90 allocated to the matched control group. The remainder of this section describes the sampling procedures followed within each village.

In each village, two dusuns were sampled. At baseline it was not clear which dusuns the project would work in and as such the evaluation selected one dusun randomly as well as including the dusun in which the village head’s office was located. The rationale for the selection of the dusun with the village head’s office was that it would have a higher concentration of people and also be a likely location for early childhood services. We felt confident about detecting project participation without yet knowing about project placement as the intervention aimed to have an influence at the village level. On average there are five dusuns per village [28].

Households were randomly selected during the baseline survey from a listing that was created for this evaluation. As individual level enumeration data is not available for Indonesia, the World Bank had to construct a listing. To construct this listing, fieldworkers went to each village, met the village and dusun heads, and asked for a resident roster list of all households by dusun where there was a child aged between 0 and 6 years. In some areas, if the information from the dusun head was incomplete or questionable, this information was cross-checked with records from the posyandu head (integrated child health services clinic) and/or a midwife. In each dusun, survey teams interviewed ten households with children aged 1 and/or 4 years, amounting to 20 households per village and thus 6,200 households in total.

In the case where a sampled dusun had an insufficient number of children in the target ages, field teams randomly selected another dusun, and continued this random selection process until meeting the required 20 households per village. If all the households with children in the target age range as per the listing had been contacted across the entire village, but the survey team still had not interviewed 20 households, then supervisors could ask people in the village if there were other children in the village that met the age criteria (that is, snowballing), and interview them.

The objective of sampling households with children aged 1 and/or 4 years in each village was to follow children who would span the ages of 1 to 7 years during the life of the survey, capturing most of the target age range of the project. Children who were aged 1 year at baseline will have reached the age of 4 years at endline, thus providing an additional comparison with the cohort of children aged 4 years old at baseline. The cohort analysis of the children aged 1 year will provide information on the effectiveness of ECED interventions focused at very early childhood, mostly related to health (nutrition, vaccinations, fine motor skills and gross motor skills) and parenting. Children who were aged 4 years old at baseline will be around 7 years old at endline, and will most likely be enrolled in the early years of primary school. At this point, this cohort will have reached an age where we can assess school performance, and shed light on the project’s impact on increasing school readiness. The analysis based on the older age cohort will provide information on the effectiveness of the ECED interventions aimed at children in the age range of 4 to 6 years old.

#### Midline replacement procedures

Since this study aimed to track the same children over three rounds of data collection, the study team made every attempt to interview the baseline children again at midline in 2010. Across all nine districts, 112 children were not reached in the midline. The most common reasons for a child not being available for midline interview were: the household was impossible to find (17 children), the child had died (nine children), the family refused (five children) or other reasons (81 children).

In the case of children moving, field teams adhered to the following protocol. First, the teams tried to assess whether the child had moved to another village (in the same district) that was in the study sample. If the child had, the child and household were interviewed in the new village. One hundred and one of the children had moved to another village prior to midline, but were able to be identified and interviewed in their new village. Second, if tracking a child to a sample village was impossible, the household was replaced using the same identification procedure from the baseline. The field teams used the dusun level listing from the two sample dusuns, and if this listing did not yield 20 households per village, then the field teams used the procedure outlined above for randomly selecting a new dusun. While replacements were made, the reason for them was not always recorded, and the exact number of children who had moved to another village and were no longer able to be tracked is unknown.

Other reasons for replacing or adding new households included: i) baseline teams had erred in interviewing children in the wrong age group in baseline; or ii) baseline teams were not able to identify 20 households with children who met the age criteria, and thus teams in the midline attempted to search again and add households. While tracking children outside of a sample area might have been possible, the research team decided against it for reasons of cost and questionable benefit to the evaluation. All children who were lost to follow-up at midline were replaced. The participant flow diagram (Figure 1) provides details regarding the number of children lost to follow-up in each study district.

